### **Efficacy Analysis**

***Aim 2: What are the potential effects of technological visual training in PwP and how do they compare to standard visual training techniques?***

The main focus of this aim of the study is to determine how the two treatments (TVT and standard care) influence participant outcomes over time, particularly visuomotor performance.

For this aim, data for the primary efficacy outcome (TMT) and secondary outcomes (balance, gait etc.) will be analysed using repeated measures analysis of covariance (ANCOVA), comparing the pre-intervention to post-intervention outcome. The dependent variable will be the outcome of interest (i.e., TMT), with age, gender, disease duration and H&Y stage as covariates. In case of any missing data, sensitivity analysis (last observation carried forward) will be used with delta-adjusting imputation.

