### **ASSESSMENTS**

A repeated measure design will be employed with assessments performed at the clinical gait lab on two separate sessions lasting between 2-3 hours. Participants will attend the lab for outcomes to be measured at the start (baseline) and at the end of the first 4 week intervention. Results will be compared between the groups.

1. Baseline assessment (up to 180 mins)
  - Initial screening and standard clinical assessments
  - Sensorimotor assessment using Senaptec Sensory Station (SSS)
2. Follow-up assessment (after 4 week intervention) (up to 180 mins)
  - Standard clinical assessments
  - Sensorimotor assessment using Senaptec Sensory Station (SSS)

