### **OUTCOMES**

For the purposes of this study, feasibility will be explored in relation to safety and acceptability of the TVT intervention. See *Appendix 20* for full description of feasibility outcomes for the study.

To estimate the potential effects of TVT in PwP, a set of clinical outcomes relevant to PwP will be assessed. The primary clinical outcome will be change in visual attention from baseline to follow-up assessed with the Trail Making Test and the Senaptec Sensory Station.

Secondary clinical outcomes will be changes in balance and gait, mobility, physical endurance, quality of life, cognition and falls-efficacy. Gait and balance characteristics will be recorded via wearable

sensors (e.g. accelerometers) used during standing and walking under different conditions (including but not limited to single and dual tasks). Spatiotemporal gait characteristics (e.g., gait speed (m/s), variability (CV%), step/stride length (m), stride time (s), swing time (%), asymmetry, and step width (cm)) will be determined. Balance characteristics will include sway area (mm^2), sway path length (mm) and sway velocity (mm/s).

Additional measures will be used to describe the characteristics of the participants in terms of disease status, multimorbidity and mood.

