## **Statistical Analysis**

Statistical analysis will be undertaken using SPSS (v.26, IBM). All statistical tests will be carried out at the 5% two-sided level of significance. Demographic characteristics and baseline data will be summarized using descriptive statistics, including means, standard deviations, median, minimum, maximum and inter-quartile ranges for continuous or ordinal data and percentages for categorical data. The descriptive statistics will be tabulated and presented graphically for clarity.

The statistical methods to be used are outlined in the following paragraphs;

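### The efficacy model does not adjust for the baseline score, so the arm comparison, though unbiased under randomisation, loses precision and over-corrects for chance baseline imbalance

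*Protocol*

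**What the plan says.** The Efficacy Analysis section (Aim 2) of the protocol specifies "repeated measures analysis of covariance (ANCOVA), comparing the pre-intervention to post-intervention outcome". The outcome itself, for example the Trail Making Test (TMT), is the dependent variable, and the model is fitted "with age, gender, disease duration and H&Y stage as covariates". The same analysis serves the secondary outcomes.

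The Assessments section fixes the number of time points: "A repeated measure design will be employed with assessments performed at the clinical gait lab on two separate sessions", one at baseline and one after the four-week intervention, with results compared between the groups. The Outcomes section is consistent with a change-score analysis: "The primary clinical outcome will be change in visual attention from baseline to follow-up". The Statistical Analysis section adds "All statistical tests will be carried out at the 5% two-sided level of significance".

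The baseline score therefore enters only as the first of the two repeated values. No other section adds it as a covariate. Because the covariates are named one by one, this is a choice that the protocol makes, not a detail left to a later analysis plan.

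**The concern.** With two visits, the group-by-time term of this model is the coefficient of arm in a regression of change (follow-up minus baseline) on arm and the four covariates. Such a comparison treats the baseline score as if each unit of it carried over fully to follow-up. When the correlation between visits is below 1, it carries over only in part. Two things follow.

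First, noise in the baseline score is added to the outcome instead of being used to explain it, so the confidence interval is wider than it need be. Second, the arm that happens to start worse tends to show more improvement by regression to the mean, and the estimate moves in its favour.

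Both matter more in a small trial. The Participants section describes 20 per arm allocated by a random number generator, with no stratification on baseline score. Aim 2 asks whether the technological training gives greater benefit than standard care, so the between-arm estimate is a result that readers will use.

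**Working it through.** **Inputs.** From the protocol: 20 per arm, two visits, two-sided 5% tests, four covariates. The protocol gives no SD, effect size or correlation between visits, so there is no stated figure to reproduce. Assumptions: equal SD at both visits, set to 1; correlation r from 0.3 to 0.9; and, where power is shown, a true effect of 0.5 SD.

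**Precision.** Ignoring the four covariates:

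- variance of a change score = 2(1 − r)
- residual variance of follow-up given baseline = 1 − r² = (1 − r)(1 + r)
- ratio = 2/(1 + r)
- participants under baseline-adjusted ANCOVA with the same precision as 40 under the plan = 40(1 + r)/2
- ratio of CI widths = √(2/(1 + r))

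Power (normal approximation) = Φ(0.5/(s√(2/20)) − 1.96), with s² = 2(1 − r) for the plan and 1 − r² for ANCOVA.

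| r (assumed) | Variance ratio | Equivalent n of 40 | CI width ratio | Power, plan | Power, ANCOVA |
|---|---|---|---|---|---|
| 0.3 | 1.54 | 26 | 1.24 | 27% | 38% |
| 0.5 | 1.33 | 30 | 1.15 | 35% | 45% |
| 0.7 | 1.18 | 34 | 1.08 | 53% | 60% |
| 0.8 | 1.11 | 36 | 1.05 | 71% | 75% |
| 0.9 | 1.05 | 38 | 1.03 | 94% | 95% |

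The protocol claims no power; those columns only illustrate the scale.

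**Chance imbalance.** Let D be the observed baseline difference between arms and δ the true effect. Given D, the expected follow-up difference is δ + rD. Subtracting D gives an expected change-score difference of δ − (1 − r)D, whereas the baseline-adjusted estimate has expectation δ. The standard error of D is √(2/20) = 0.32 SD. For D of one standard error, the shift (1 − r) × 0.316 is:

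- r = 0.5: 0.16 SD
- r = 0.7: 0.09 SD
- r = 0.8: 0.06 SD

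The shift is always towards the arm that started worse. TMT is timed in seconds, so that is the slower arm at baseline.

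**Do the four covariates stand in for baseline?** A simulation used 20 per arm, a 0.5 SD effect, 8,000 trials per value of r, and four covariates assumed to explain 20% of the outcome variance, included in both models.

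| r | Variance ratio | Power, plan | Power with baseline | Slope on baseline imbalance, plan | Slope with baseline |
|---|---|---|---|---|---|
| 0.5 | 1.40 | 31% | 41% | −0.64 | about 0 |
| 0.7 | 1.21 | 47% | 54% | −0.39 | about 0 |
| 0.8 | 1.10 | 63% | 67% | −0.24 | about 0 |

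The loss and the dependence on imbalance remain with the covariates in the model. Both estimates averaged about 0.50, the true effect, so neither is biased over repeated randomisations.

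**The case against.** The strongest reply is that the planned analysis is valid. Group-by-time in a randomised two-visit trial is unbiased, and its confidence interval already allows for chance imbalance. At r = 0.7 the standard error of the change contrast is √(2 × 0.6/20) = 0.24 SD, so a shift of 0.09 SD is about 0.4 of a standard error. The Sample Size section says that the trial does not set out to assess efficacy formally, and no decision rule rests on the 5% tests. The size of the loss depends on an r that the protocol does not give. The large-sample guarantee for ANCOVA is not exact at n = 40; the simulation, which includes the cost of estimating the baseline slope, was not run at r = 0.9, where the algebraic gain is only 5%. All of this stands, and it limits the point to a recommendation.

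It could also be said that the term ANCOVA already implies baseline adjustment. The wording does not support that: the covariates are listed, baseline is not among them, and the pre-intervention score is part of the repeated outcome.

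Some stronger readings are tempting but not supported:

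- A reader might infer that a pre/post contrast mixes in the practice gain on a repeated timed test. The Assessments section and the Aim 2 question both call for comparison between groups, where a gain common to both arms cancels.
- A reader might fear that the group main effect, which averages baseline with follow-up, will be reported as the treatment effect. Nothing in the protocol says so.
- A reader might think that the plan forfeits parameters needed to size the main trial. The two visits give both SDs and their correlation whichever model is fitted.

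**Conclusion.** The point holds as one of efficiency and of sensitivity to chance imbalance. The plan does not produce a biased treatment effect, nor does it leave the raw baseline difference in the estimate: it removes too much of it.

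The cost is material if the correlation between visits is about 0.3 to 0.7 (variance larger by 54% down to 18%), modest at 0.8 (11%) and small at 0.9 (5%). These figures assume equal variances at the two visits and leave out the other covariates; with four moderately prognostic covariates included, the simulated ratios at 0.5 to 0.8 were similar. The change is worth making because the better analysis uses a measurement already scheduled, but the planned one would not invalidate the trial.

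**What to change.** In the Efficacy Analysis section, replace the repeated-measures model. For TMT and each continuous secondary outcome, fit a linear model with the follow-up value as dependent variable, arm as the factor of interest, the baseline value of the same outcome as covariate, and the four listed covariates kept. State that the result is the adjusted between-arm difference with its 95% CI, and that within-arm changes are descriptive.

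The definition of the primary clinical outcome as a change can stay: with baseline in the model, regressing change or the follow-up value gives the same arm estimate.

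The cost is revised wording and one residual degree of freedom (from 34 to 33 with 40 complete cases and Hoehn & Yahr stage as a single term). No new assessment is needed, and the model can be fitted in the software already named.

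### The efficacy model omits the outcome's own baseline value as a covariate, so its arm-by-time test is a change-score comparison: valid, but less precise than the same data allow

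*Protocol*

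**What the plan says.** Under Efficacy Analysis, the protocol states that the Trail Making Test and the secondary outcomes "will be analysed using repeated measures analysis of covariance (ANCOVA), comparing the pre-intervention to post-intervention outcome". The next sentence completes the model: the outcome itself is the dependent variable, "with age, gender, disease duration and H&Y stage as covariates". The list is explicit, and the baseline value of the outcome is not on it. Baseline enters only as one of the two repeated responses, and no other section adds it as a covariate.

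Three other places bear on the point:

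- ASSESSMENTS fixes two measurement occasions, with "outcomes to be measured at the start (baseline) and at the end of the first 4 week intervention", and adds: "Results will be compared between the groups".
- OUTCOMES defines the endpoint as a change: "The primary clinical outcome will be change in visual attention from baseline to follow-up assessed with the Trail Making Test and the Senaptec Sensory Station".
- Statistical Analysis sets the testing level: "All statistical tests will be carried out at the 5% two-sided level of significance".

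Efficacy Analysis does not name the term of the model that carries the treatment comparison.

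**The concern.** For a timed test, a gait measure or a balance measure, the same measure at baseline is usually among the best predictors of the follow-up value. The trial collects it on everyone, yet the model uses it only by subtraction.

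Subtraction amounts to fixing the slope of follow-up on baseline at 1. When the true slope is below 1, this over-corrects. An arm that starts worse by chance drifts back toward the mean and appears to improve more.

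Two things are at stake. The interval for the difference between arms is wider than it need be, and the estimate depends on whatever baseline imbalance chance produces. With 20 per arm, allocated by a random number generator and with no stratification on the outcome described, imbalances of some size are to be expected.

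**Working it through.** **Inputs.** From the protocol: 40 participants, 20 per arm; two time points; four covariates, none of them the baseline outcome; two-sided 5% level. The protocol gives no effect size, SD or power, so there is no figure of its own to reproduce. Assumed: an equal SD σ at both visits and a baseline to follow-up correlation ρ of 0.5 to 0.9.

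**Step 1: what the arm-by-time term is.** With two time points and covariates measured once per person, differencing the two responses removes every person-level term that is constant over time. What remains is a regression of (follow-up − baseline) on arm and the four covariates. A numerical check on one simulated data set gave t = 0.73686 and an estimate of 0.1592 from both the repeated measures model and the change-score regression.

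**Step 2: precision.** With n = 20 per arm:

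- change score: variance = 2σ²(1−ρ) × 2/n
- baseline-adjusted: variance = σ²(1−ρ²) × 2/n
- ratio, adjusted to change = (1−ρ²) / [2(1−ρ)] = (1+ρ)/2

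The extra parameter costs a factor of roughly 1 + 1/(40−6−2) = 1 + 1/32 = 1.031. The 6 counts the intercept, arm and four covariates. Standard errors below are in SD units.

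| ρ (assumed) | SE, change | SE, adjusted | Variance ratio | Ratio × 1.031 | Adjusted N matching 40 by change score |
|---|---|---|---|---|---|
| 0.5 | 0.316 | 0.274 | 0.75 | 0.77 | 30 |
| 0.7 | 0.245 | 0.226 | 0.85 | 0.88 | 34 |
| 0.8 | 0.200 | 0.190 | 0.90 | 0.93 | 36 |
| 0.9 | 0.141 | 0.138 | 0.95 | 0.98 | 38 |

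The last column is 40 × (1+ρ)/2, before the degree-of-freedom cost.

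**Step 3: simulation with the four covariates in both models.** There were 4,000 trials per setting with 20 per arm, a true difference of 0.5 SD, and covariates explaining 0, 20 or 40% of the outcome variance. The loss of a degree of freedom is included.

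| ρ | Change-score variance ÷ adjusted variance | Power, change score | Power, adjusted |
|---|---|---|---|
| 0.5 | 1.30 to 1.61 | 30 to 31% | 37 to 47% |
| 0.7 | 1.17 to 1.29 | 46% | 50 to 58% |
| 0.9 | 1.01 to 1.04 | 90% | 90 to 91% |

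**Step 4: sensitivity to chance imbalance.** With 20 per arm, the baseline difference has standard error √(2/20) = 0.316 SD. Given an observed baseline difference D, the follow-up difference is expected to carry ρD. The change-score difference therefore carries ρD − D = −(1−ρ)D, and the adjusted difference carries about zero. The simulated slopes agree: about −0.5, −0.3 and −0.1 for the change score at ρ = 0.5, 0.7 and 0.9, and about 0 for the adjusted estimate.

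For an imbalance of one standard error, the size of the shift is:

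- ρ = 0.5: 0.5 × 0.316 = 0.16 SD
- ρ = 0.7: 0.3 × 0.316 = 0.09 SD
- ρ = 0.9: 0.1 × 0.316 = 0.03 SD

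**The case against.** The strongest defence is that the stated analysis is inefficient rather than wrong. It subtracts baseline, so it does not ignore it, and it matches an endpoint defined as change. In a randomised trial the change-score contrast is unbiased and its test is valid. The shift in Step 4 is conditional on the imbalance that happens to occur; it is not a bias over repeated randomisation. All of this stands.

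It also stands that the size of the gain rests on a correlation the documents do not give. For a highly repeatable measure the gain all but disappears. The study is moreover a pilot: feasibility is its first aim, and SAMPLE SIZE says it is not meant as a formal test of efficacy. No decision rule hangs on this test.

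Three stronger readings are tempting, and the documents do not support them.

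- A reader might infer that an inflated variance would be carried into the main-trial sample size. SAMPLE SIZE does not say which variance would be used. The SDs and the correlation between visits can be computed from the same data whichever model is fitted.
- A reader might infer that every arm comparison from this model is a change-score comparison. That is exact only for the arm-by-time term. The group main effect compares the average of the two visits. It is no better a treatment estimate: in the simulation it recovered about 0.25 of a true 0.50 SD.
- A reader might take the missing covariate for a detail left to a separate analysis plan, or hold that ANCOVA implies baseline adjustment. The protocol states a repeated measures model and lists its covariates. If adjustment was intended, the sentence needs the same correction.

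**Conclusion.** The point holds as a nearly free improvement to a valid analysis. If the treatment effect is read from the arm-by-time term, it is exactly a comparison of mean change adjusted for the four listed covariates.

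Baseline adjustment would reduce its variance to 0.75 of that value at ρ = 0.5, 0.85 at 0.7, 0.90 at 0.8 and 0.95 at 0.9, before the cost of one degree of freedom. The gain is material at 0.5 to 0.7 and negligible near 0.9. Adjustment would also remove nearly all of the conditional dependence on chance imbalance, which at one standard error is worth 0.16 SD at ρ = 0.5 and 0.03 SD at ρ = 0.9.

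These figures rest on equal SDs at the two visits, a linear relation between them, complete data on 20 per arm, and the assumed values of ρ. The algebra in Step 1 does not depend on ρ.

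**What to change.** In Efficacy Analysis, state that the between-arm comparison of each continuous clinical outcome uses a linear model of the follow-up value on arm, the baseline value of that same outcome and the covariates already listed. State that the arm coefficient is the treatment effect, reported with its 95% CI. Change within each arm can still be reported descriptively, which keeps the protocol's interest in change over time.

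The cost is one sentence and one degree of freedom. No new data are needed, and randomisation, visits and measures stay as they are.

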## **INTERVENTIONS**

Following screening and clinical assessment at the Gait Lab, participants will receive a telephone call from the researcher prior to starting the visits. This will allow participants to ask any further questions about the sessions following their assessments and to help them feel more familiar with the visiting therapist. It will also be an opportunity for the researcher to help the participant identify a suitable location in their home in which to undertake the subsequent training sessions in preparation for the first visit.

After the familiarisation phone call, the home visits will commence. Participants will be allocated to either Group A (technological visual training) or Group B (standard training). Both groups will receive two training sessions per week for four weeks in their home environment delivered by one of the researchers. Following this intervention, participants will be invited back to the Gait Lab for follow-up assessment. See *Figure 1* below for a summary for the study design.

[figure not shown]

Figure 1. Study design

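### The only missing-data method named, LOCF with a delta adjustment, reduces to baseline carried forward in a one-follow-up design and is not a sound sensitivity analysis

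*Protocol*

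**What the plan says.** Protocol, Efficacy Analysis, closes its description of the model with one sentence on missing data. If any are missing, "sensitivity analysis (last observation carried forward) will be used with delta-adjusting imputation". No other imputation method is named there.

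Protocol, Assessments, provides for "assessments performed at the clinical gait lab on two separate sessions lasting between 2-3 hours": a baseline visit and one follow-up. The text reads "Participants will attend the lab for outcomes to be measured at the start (baseline) and at the end of the first 4 week intervention". The word 'first' might suggest a later period, but the list that follows contains only these two assessments and the trial is a 4-week parallel-group design.

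Protocol, Outcomes, defines the primary clinical outcome as "change in visual attention from baseline to follow-up assessed with the Trail Making Test and the Senaptec Sensory Station". Efficacy Analysis applies "repeated measures analysis of covariance (ANCOVA), comparing the pre-intervention to post-intervention outcome". Under Interventions, "Both groups will receive two training sessions per week for four weeks in their home environment".

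**The concern.** LOCF is usually applied to repeated post-baseline visits. Here there is one, so a participant who misses it has nothing to carry forward except baseline, and LOCF then asserts that this participant did not change. That is an implausible default in either arm, because both train actively for eight sessions and both repeat a timed test.

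Delta adjustment asks how far the missing outcomes would have to differ from what a missing-at-random model predicts before the conclusion changes. It needs such a model underneath. A carried-forward baseline is not one: delta = 0 then means no change, rather than missing at random.

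What is at stake is whether the sensitivity analysis can say anything about robustness. It would also report a precision that the data do not support.

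**Working it through.** The protocol states no delta, dropout rate, SD or effect size, so there is no figure of its own to reproduce. The check is algebra, then an illustration on assumed inputs.

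**1. What LOCF imputes.** Let Y0 be baseline and Y1 the single follow-up. If Y1 is missing, LOCF sets Y1 = Y0, so change = Y1 − Y0 = 0. Adding delta gives change = delta for every missing participant in the arm. The imputed changes have zero variance, so no imputation uncertainty enters. LOCF also cannot fill a missing baseline, although the sentence covers any missing data.

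**2. Effect on the estimated difference.** Count improvement as positive. Let c be the mean improvement in control, e the extra improvement in TVT, pT and pC the fractions missing (completely at random), and d a common improvement assigned to missing participants (d = 0 is plain LOCF). The expected estimate is

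(c + e)(1 − pT) − c(1 − pC) + d(pT − pC).

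Assumed, not from the protocol: c = 10 s, and e = 5 s or 0. With d = 0:

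| Missing TVT / control | True effect 5 s | True effect 0 |
|---|---|---|
| 5% / 5% | 15×0.95 − 10×0.95 = 4.75 | 0 |
| 20% / 20% | 15×0.80 − 10×0.80 = 4.0 | 0 |
| 20% / 5% | 15×0.80 − 10×0.95 = 2.5 | 8 − 9.5 = −1.5 |
| 5% / 20% | 15×0.95 − 10×0.80 = 6.25 | 9.5 − 8 = 1.5 |

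Equal dropout p shrinks the effect to e(1 − p). Unequal dropout moves it either way.

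**3. With a delta.** At 20% / 5% missing the term is 0.15d. With d = 5 s the estimates are 2.5 + 0.75 = 3.25 and −1.5 + 0.75 = −0.75. With d = 10 s they are 4.0 and 0. With equal dropout a common d cancels, so the attenuation stays. Deltas set to the assumed arm means restore the truth: (12 + 15×0.20) − (9.5 + 10×0.05) = 15 − 10 = 5 s. That supplies by hand the reference that LOCF lacks.

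**4. Simulation with the ANCOVA.** Settings: 20 per arm, baseline-adjusted ANCOVA, two-sided 5%, 6,000 runs per scenario. Assumed: SD 1, baseline to follow-up correlation 0.7, improvement of 0.5 SD in both arms, delta = 0, data missing completely at random.

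| Missing TVT / control | LOCF estimate, true effect 0.50 SD |
|---|---|
| 5% / 5% | 0.48 |
| 10% / 10% | 0.45 |
| 20% / 20% | 0.40 |
| 20% / 10% | 0.35 |
| 20% / 0% | 0.30 |

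Complete-case ANCOVA gives 0.50 to 0.51 throughout. With no true effect, LOCF shows 0.05 SD against TVT at 10% / 0% or 20% / 10% missing, and 0.10 SD at 20% / 0%, where it rejects in 6.9% of runs.

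**5. Precision.** At 20% / 20% missing and no effect, the mean LOCF standard error is 0.217, against 0.255 for complete cases. Fully observed data would give about √(0.51×2/20) = 0.226, where 0.51 = 1 − 0.7². Losing a fifth of the follow-ups therefore appears to give more precision than losing none.

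**The case against.** The strongest reply has four parts.

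- **It is only a sensitivity analysis.** A reader might infer that missing data bias the main result. The protocol does not support that. Efficacy Analysis uses the word sensitivity, does not fix how missing values enter the main ANCOVA, and may leave that to an analysis plan not shown here. This stands: the figures above describe the sensitivity result only.
- **The wording is open.** It can mean delta added to carried-forward values, or LOCF alongside a separate delta-adjusted imputation. A reader might infer that the two methods are incompatible on any reading. That goes too far. On the second reading they are not joined, and on the first a fixed shift from no change is still a defined scenario. On either reading, however, the LOCF component is baseline carried forward.
- **The sizes rest on chosen inputs.** The tables set delta to 0, and a suitable common delta removes the spurious difference at 20% / 5%. The Recruitment section expects low attrition. Strobe intolerance might suggest heavier loss in TVT, but the exclusion criteria remove people with light sensitivity, migraine or epilepsy, Safety Considerations lets participants try the glasses first, and not tolerating training is different from missing the follow-up visit. All of this stands, and it limits the size.
- **It is a pilot.** Sample Size says that formal efficacy is not the purpose. A reader might also infer that LOCF would distort the SD used to plan the main trial. No calculation shows this, and nothing in the protocol says that the SD would come from imputed data.

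Nor do the small standard errors by themselves inflate false positives. With equal 20% missingness and no effect, LOCF rejected in 3.8% of runs. The 6.9% comes from the shifted estimate.

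**Conclusion.** The point holds for the sensitivity analysis. That missing changes become exactly 0 or exactly delta follows from the two-visit schedule and needs no assumption, and neither does the lack of imputation variance or of a missing-at-random anchor. This is a stated rule that does not fit the design, rather than detail left for later.

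The size depends on assumed improvement, effect, dropout and delta. With delta = 0 it runs from negligible at 5% missing per arm (4.75 s for an assumed 5 s) to half the effect at 20% / 5%, or an overstatement of 1.25 s with those rates reversed. LOCF is therefore not reliably conservative. In the simulated scenarios its standard error was never above that of the complete cases.

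Severity is should-fix. The flaw lies in a sensitivity analysis, attrition is expected to be low, and the pilot does not claim a formal test of efficacy.

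**What to change.** In Protocol, Efficacy Analysis, replace the missing-data sentence with wording to this effect: if outcome values are missing, the sensitivity analysis will use multiple imputation under missing-at-random, with arm, baseline outcome and the model covariates as predictors. The delta adjustment will be applied to those imputations over a stated range of deltas, varied by arm. Keep LOCF, if at all, only as a separately labelled no-change scenario.

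Entering arm as a predictor avoids fitting separate models to very few participants: at 20% missing, an arm of 20 has 16 observed follow-ups. The cost is one sentence and a little more analysis work. Visits, sample size and data collection do not change.
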